### 2.8. Secondary Outcomes

#### 2.8.1. Sepsis

Neonatal sepsis, a frequently encountered clinical syndrome in newborns, is associated with elevated morbidity and mortality rates. Current research highlights the major regulatory role of vit D in the immune system, which is capable of impeding cell proliferation and maturation while also controlling inflammatory cytokines [21]. Sepsis is defined as a clinical condition, the cause of which is a systemic inflammatory reaction of the body arising because of bacterial infection, primarily under the influence of released bacterial toxins and fragments constituting bacterial components. Research findings indicated a significant association between neonatal sepsis and low levels of vit D in both cord blood and maternal blood [22]. Late-onset sepsis is defined as blood culture-proven and/or clinical sepsis occurring after 3 days of age [18]. Per the guidelines of the Polish Society of Neonatology, the initial suspicion of sepsis is based on the presence of at least two of the following clinical symptoms: apnea, elevated body temperature, signs of respiratory distress syndrome, hypoxia, feeding reluctance, somnolence, or overstimulation. Positive laboratory test results further support the suspicion. The confirmation of a diagnosis is a positive bacteriological blood test result from one blood sample of at least 1 mL [23]. Neonatal staff will collect venous samples (1 mL) for a bacteriological blood test and laboratory tests. Laboratory tests include morphology with smear; if any sepsis risk factor exists, the findings will have an immature-to-total neutrophil ratio (I:T) >0.2 and levels of C-reactive protein (CRP) >10 mg/L, procalcitonin (PCT) >0.5 ng/mL, and interleukin 6 (IL-6) >44 pg/mL [23,24].

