## Abstract

Vitamin D deficiency can escalate prematurity bone disease in preterm infants and negatively influence their immature immunology system. Infants born at 24 + 0/7 weeks to 32 + 6/7 weeks of gestation will be considered for inclusion. Cord or vein blood samples will be obtained within 48 h after birth for 25-hydroxyvitamin D level measurements. Parathyroid hormone and interleukin-6 levels will be measured. Infants will be randomized to the monitored group (i.e., an initial dose of 1000 IU/day and possible modification) or the controlled group (i.e., 250 IU/day or 500 IU/day dose, depending on weight). Supplementation will be monitored up to a postconceptional age of 35 weeks. The primary endpoint is the percentage of infants with deficient or suboptimal 25-hydroxyvitamin D levels at 28 ± 2 days of age. 25-Hydroxyvitamin D levels will be measured at postconceptional age 35 ± 2 weeks. Secondary goals encompass assessing the occurrence of sepsis, osteopenia, hyperparathyroidism, and interleukin-6 concentration. The aim of this study is to evaluate the efficacy of monitored vitamin D supplementation in a group of preterm infants and ascertain if a high initial dosage of monitored vitamin D supplementation can decrease the occurrence of neonatal sepsis and metabolic bone disease.

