## 2. Materials and Methods

### 2.1. Study Design

We are implementing an unblinded, parallel-group, randomized controlled superiority trial. Parents of neonates born between 24 + 0/7 weeks and 32 + 6/7 weeks of gestation will be offered the opportunity to participate in the study within the first 24 h of the infant’s life. After providing information orally and in writing concerning the study, we will seek written consent from the parents for the neonate and mother to participate in the trial. To enhance the relevance of the research findings, we will stratify the study group by gestational age into 24–28 and 29–32 weeks of gestation subgroups. We have planned to recruit for the study for 36 months, from September 2024 to the end of 2027. The study protocol has been registered at ClinicalTrials.gov (identifier: NCT06199102). Please see Table 1 for all planned patient-related activities.

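### In an unblinded trial, section 2.8.1 pools culture-proven with clinical, culture-negative late-onset sepsis, so a difference in the pooled rate could partly reflect labelling

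*Protocol article*

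**What the plan says.** All of the following is in the protocol article.

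- Design (2.1): "We are implementing an unblinded, parallel-group, randomized controlled superiority trial".
- Event definition (2.8.1): "Late-onset sepsis is defined as blood culture-proven and/or clinical sepsis occurring after 3 days of age".
- Start of suspicion (2.8.1): "the initial suspicion of sepsis is based on the presence of at least two of the following clinical symptoms". Seven signs are listed. Apnea, raised temperature and hypoxia can be measured or monitored. Feeding reluctance, somnolence and overstimulation are more a matter of judgement.
- Laboratory tests (2.8.1): "Positive laboratory test results further support the suspicion". The markers are the immature-to-total neutrophil ratio, CRP, "procalcitonin (PCT) >0.5 ng/mL, and interleukin 6 (IL-6) >44 pg/mL".
- Confirmation (2.8.1): "The confirmation of a diagnosis is a positive bacteriological blood test result from one blood sample of at least 1 mL".
- Culture at suspicion (Table 1 footnote): a blood culture of at least 1 mL is taken whenever late-onset sepsis is suspected.
- Status of the outcomes (Abstract): "Secondary goals encompass assessing the occurrence of sepsis, osteopenia, hyperparathyroidism, and interleukin-6 concentration". Reducing sepsis is also part of the stated aim in the Abstract, the Introduction and the Discussion.
- Masked assessment: stated only for the renal ultrasound readers (2.9.1).

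**The concern.** The definition admits two kinds of case that differ in how far they depend on opinion. A positive culture is a laboratory result. A clinical-only case depends on someone deciding that the signs and markers amount to sepsis, and in this trial that person may know which arm the infant is in. If the threshold for that decision differs between arms, the pooled rate differs even when proven infection does not.

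The section makes a positive culture the confirmation but does not make confirmation a condition for counting as an event. A reader of the results would see one sepsis rate and could not tell which kind of case drove a difference. That matters because reduced sepsis is one of the two clinical benefits named in the aim.

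**Working it through.** **The plan's own figures.** The document gives no sample-size or power figure for sepsis. The group size comes from the primary endpoint (section 2.12: 80% versus a decrease of 25 points to 55%, power 80%, α = 0.05). With a two-sided test and pooled variance:

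n = [1.960 × √(2 × 0.675 × 0.325) + 0.842 × √(0.80 × 0.20 + 0.55 × 0.45)]² / 0.25² = 53.9, so 54 per group.

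This reproduces the stated 54. The total of 130 is 65 per group. The figures of 54 and 65 are used below only as group sizes.

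**What counts as an event.**

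1. Under the definition sentence, culture-proven cases count and clinical culture-negative cases count.
2. Under the confirmation sentence, only a positive culture confirms.
3. The two can stand together if the second says only what makes a case proven. In that reading clinical-only cases remain in the pooled event.
4. Clinical-only cases start from at least two signs, in an open trial, with no masked classification stated.

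**What labelling alone could do (illustration).** The split between proven and clinical-only sepsis is not in the document, so every rate here is an assumption:

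- Culture-proven rate c, equal in both arms: 8%, 14% or 20%. The Introduction cites 8–20% for sepsis in preterm and low-birth-weight infants without saying which definition that range uses.
- Clinical-only rate k in controls: 10% or 20%.
- Relative reduction r in clinical-only labels in the monitored arm, from labelling alone: 25% or 50%.

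Pooled rate in controls = c + k. Pooled rate in the monitored arm = c + k(1 − r). Relative risk (RR) = the second divided by the first. The last column is the normal-approximation chance of two-sided p<0.05 favouring the monitored arm, at 54 and 65 per arm. It would be 2.5% with no labelling difference.

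| c | k | r | Control | Monitored | RR | Chance at 54; 65 |
|---|---|---|---|---|---|---|
| 8% | 10% | 25% | 18.0% | 15.5% | 0.86 | 5.3%; 5.7% |
| 8% | 10% | 50% | 18.0% | 13.0% | 0.72 | 10.7%; 12.0% |
| 8% | 20% | 25% | 28.0% | 23.0% | 0.82 | 8.6%; 9.5% |
| 8% | 20% | 50% | 28.0% | 18.0% | 0.64 | 23.3%; 27.1% |
| 14% | 10% | 25% | 24.0% | 21.5% | 0.90 | 4.9%; 5.3% |
| 14% | 10% | 50% | 24.0% | 19.0% | 0.79 | 9.2%; 10.2% |
| 14% | 20% | 25% | 34.0% | 29.0% | 0.85 | 8.0%; 8.9% |
| 14% | 20% | 50% | 34.0% | 24.0% | 0.71 | 20.6%; 23.9% |
| 20% | 10% | 25% | 30.0% | 27.5% | 0.92 | 4.7%; 5.0% |
| 20% | 10% | 50% | 30.0% | 25.0% | 0.83 | 8.4%; 9.3% |
| 20% | 20% | 25% | 40.0% | 35.0% | 0.88 | 7.7%; 8.5% |
| 20% | 20% | 50% | 40.0% | 30.0% | 0.75 | 19.1%; 22.1% |

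The table assumes fewer labels in the monitored arm. The document gives no direction, and labelling could also run the other way.

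**How few events culture-proven sepsis would have.** At 8% to 20%, expected events per arm are 54 × 0.08 = 4.3 to 54 × 0.20 = 10.8, or 65 × 0.08 = 5.2 to 65 × 0.20 = 13. The power to detect a true halving is 14% to 31% at 54 per arm and 16% to 36% at 65 per arm.

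**The case against.** **The section reads naturally as a sequence.** Signs raise suspicion, laboratory tests support it, and culture confirms it. This stands: the two sentences need not contradict each other, and they should not be reported as an error. What remains is that the pooled definition counts unconfirmed cases. Separate reporting might be specified in the full protocol or the SAP, but the definition given here is a single event.

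**IL-6.** A reader might infer a circular outcome: vitamin D lowers IL-6, IL-6 enters the diagnosis, so treatment removes sepsis cases by definition. The document does not support that. IL-6 is one of four markers, and they only support a suspicion that starts from clinical signs. Nothing says that "interleukin 6 (IL-6) >44 pg/mL" makes a diagnosis or that a lower value removes one. Section 2.8.1 speaks of vitamin D and inflammatory cytokines in general, without naming IL-6 or a direction. That IL-6 is both a supporting marker and a secondary outcome is a minor point. A reader might also infer that samples taken on suspicion (2.8.4) enter the comparison of IL-6 between arms. The article does not say so.

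**The signs are not all soft.** This stands: two signs are required and several can be measured, which limits the room for labelling but does not close it.

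**The magnitudes are assumptions.** This also stands. In most scenarios the pooled result would not reach significance. At 65 per arm, for example, 25% versus 20% gives RR 0.80 with an approximate 95% CI of 0.42 to 1.52.

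**Culture is not immune.** Cultures are taken when unblinded staff suspect sepsis, and a single culture can miss true cases. Culture-proven sepsis is therefore less exposed to open assessment, not free of it. With so few expected events, replacing the pooled outcome outright would be a trade-off rather than a clear gain.

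**Conclusion.** The point holds as a weakness in how a secondary outcome is defined. In an unblinded trial, the pooled sepsis rate mixes a laboratory-confirmed event with one that depends partly on judgement, so a difference between arms could partly reflect labelling.

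How large that part would be cannot be determined from the document. The relative risks of 0.92 to 0.64 show only that a visible difference is arithmetically possible without any change in proven infection. They rest wholly on the assumed rates and the assumed direction. They do not show that the trial will report a false sepsis effect.

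The primary 25(OH)D endpoint and its sample size are unaffected. The change is worth making because reduced sepsis is in the stated aim and the remedy uses cultures already planned.

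**What to change.** In section 2.8.1, state that:

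1. culture-proven late-onset sepsis (from the culture of at least 1 mL already taken at each suspicion) and clinical culture-negative sepsis are analysed and reported separately by arm;
2. the pooled rate is supportive;
3. no claim of reduced sepsis is made from the pooled or clinical-only rate unless the culture-proven result supports it.

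As an optional clarification, section 2.8.4 could say that the IL-6 comparison between arms uses the scheduled samples.

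The cost is wording only: no new samples, visits or infants. The downside is that a sepsis claim would depend on an outcome with few events and a wide confidence interval, so the trial may be unable to say much about sepsis either way. Because cultures follow suspicion, some exposure to open assessment remains.

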#### 2.8.2. Bone Mass and Biochemical Markers of MBD

Osteopenia in preterm infants occurs in approximately 20–30% of children with a birth weight < 1500 g and in 50–60% of children with a birth weight < 1000 g [11]. We have opted to define MBD as a reduction in bone mineral content compared to the anticipated level of mineralization for a fetus or infant of similar size or gestational age. This definition is coupled with observed biochemical and/or ultrasound changes. Neonatal staff will obtain venous samples of 0.7 mL for the Ca-P metabolism tests, including serum alkaline phosphatase and phosphate levels at 35 ± 1 weeks of PCA. The measurements will be performed using the AU480 chemistry analyzer (Beckman Coulter, Brea, CA, USA), which will undergo calibration checks with suitable controls following product guidelines. The mean value of these measurements will be used for data analysis.

We decided to define MBD as serum levels of alkaline phosphatase > 500 IU and serum phosphate < 1.8 mmol/L [25]. Moreover, we intend to evaluate average bone mass through the use of quantitative ultrasound (Sunlight PREMIER 7000; BeamMed, Petah Tikva, Israel). This method, deemed safe, noninvasive, radiation-free, and user-friendly, has been proposed as a screening tool for detecting osteopenia in premature infants [25,26]. Using a compact ultrasound probe (CRB probe RoHS 900–1000 kHz) positioned along the mid-tibia, this device quantifies the speed of sound (m/s) through the axial transmission mode. However, due to significant intraindividual variation, establishing normal values becomes challenging. The measurements will be made on the tibia, with the mid-tibial shaft length determined by measuring the distance from the knee to the heel. Placing the probe over the medial aspect of the mid-shaft tibia, three speed-of-sound measurements will be conducted.

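### Section 2.8.2 labels tibial speed of sound as bone mass, attaches its averaging rule to the serum chemistry, and the planned comparison ignores the gestational-age strata

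*Protocol article*

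**What the plan says.** **The label and the instrument.** Section 2.8.2 states that "we intend to evaluate average bone mass through the use of quantitative ultrasound". Later in the same paragraph it says that "this device quantifies the speed of sound (m/s) through the axial transmission mode", and it plans three such readings at the mid-tibia. It adds that "due to significant intraindividual variation, establishing normal values becomes challenging", and notes that the method "has been proposed as a screening tool for detecting osteopenia in premature infants". It gives no conversion to mass or mineral content and no cut-off in m/s. Table 1 lists a bone mass assessment at the close-out visit only.

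**The averaging rule.** The sentence "The mean value of these measurements will be used for data analysis" closes the preceding paragraph. It follows the alkaline phosphatase and phosphate samples and the chemistry analyser, and comes before the ultrasound device and its readings are described.

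**MBD.** The first paragraph says "We have opted to define MBD as a reduction in bone mineral content compared to the anticipated level of mineralization", for size or gestational age, and continues: "This definition is coupled with observed biochemical and/or ultrasound changes". The next paragraph says "We decided to define MBD as serum levels of alkaline phosphatase > 500 IU and serum phosphate < 1.8 mmol/L".

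**The analysis.** Section 2.13 assigns continuous variables to a t-test or a rank-sum test, with mean differences and 95% confidence intervals. Section 2.1 stratifies the study group into 24–28 and 29–32 weeks of gestation.

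**The concern.** The name of an outcome tends to become the name of the conclusion. The Introduction already reports the department's earlier trial this way: its quantitative ultrasound result is given as no group difference in average bone mass. If the label stays, a difference in m/s, or the absence of one, will probably again be reported as a finding about bone mass.

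Three smaller defects go with it:

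- The only averaging rule in the section is attached to the wrong measurements.
- The two statements of MBD do not say which one classifies a case. Reducing MBD is a stated aim, and the Abstract lists the occurrence of osteopenia as a secondary goal. In an unblinded trial this should be settled in advance.
- The tests named for continuous outcomes do not use the gestational-age strata, which are known at no cost and are plausibly related to bone measurements.

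**Working it through.** No figure in the article bears directly on this point, so the check is mainly a comparison of passages, with a short calculation of precision.

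**1. Named quantity against measured quantity.** The outcome is named as bone mass. The instrument output is speed of sound in m/s. In Table 1 the other assessments are blood samples for 25(OH)D, PTH and IL-6, calcium/phosphorus sampling and renal ultrasound. None yields bone mass or mineral content, so the quantity available for analysis is speed of sound.

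**2. What the mean refers to.** As placed, *these measurements* are the chemistry results. Section 2.8.2 schedules them once, at 35 ± 1 weeks PCA, which leaves nothing obvious to average. Table 1 lists calcium/phosphorus sampling at 4 weeks, 8 weeks and close-out, but a mean over visits would contradict the 35-week timing in 2.8.2. On either reading the sentence needs correcting. The three speed-of-sound readings are the only explicit replicates in the section.

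**3. Two statements of MBD.**

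| | Conceptual | Operational |
|---|---|---|
| Basis | Mineral content below the expected level | Alkaline phosphatase > 500 IU **and** phosphate < 1.8 mmol/L |
| Evidence | Biochemical **and/or** ultrasound changes | Biochemical only |
| Threshold | None given | Given |

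An infant with an abnormal ultrasound and normal chemistry is arguably a case under the first and not under the second. Only the second can be applied as written.

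**4. Precision of the arm comparison.** The inputs are two-sided α = 0.05 and power 80% (Section 2.12). The number per arm is 54, as required in 2.12, or 130/2 = 65 if no infant is lost. For two means with common SD σ:

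- Smallest detectable difference = (1.960 + 0.842) × √(2/n) × σ
- n = 54: 2.802 × 0.1925 = 0.54 σ
- n = 65: 2.802 × 0.1754 = 0.49 σ

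The article gives no σ for speed of sound, so these cannot be converted to m/s. No reference values enter the calculation.

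**5. What adjustment does.** If gestational-age stratum explains a share R² of the variance within arms, adjustment changes the variance of the arm difference from about 2σ²/n to 2σ²(1 − R²)/n. The detectable difference is multiplied by √(1 − R²). R² is not given and I do not assign it a value.

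The article suggests that R² is not zero. Section 2.8.2 puts osteopenia at 20–30% below 1500 g birth weight and 50–60% below 1000 g. Counting PCA as gestational age plus age since birth, a reading at 35 weeks falls at 35 − 24 = 11 weeks of age for the least mature infant. For the most mature it falls at 35 − 32 6/7 = 2 1/7 weeks.

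Section 2.1 mentions the strata, whereas Section 2.5 gives only 1:1 allocation in blocks of six. If randomization is stratified, an unadjusted test counts between-stratum variance that the design has removed, and its interval is too wide. If it is not, adjustment removes chance imbalance. The same analysis suits both cases.

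**The case against.** The strongest reply is that little is hidden. The paragraph that uses the label also gives the unit, the site and the number of readings, and the label is the group's shorthand from its earlier trial. Whether speed of sound is an acceptable surrogate for bone status rests on cited sources that are not at hand. A mean of the three readings is the natural intention, and an article may leave the handling of replicates, and covariates, to a fuller document. All of this has weight and keeps the point modest. It does not remove the mismatch between name and measurement. Nor is the matter simply left open: the article itself places the averaging sentence after the chemistry and names unadjusted tests.

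A reader might infer more than the article supports:

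- **That normal values are unusable.** The text calls establishing them challenging and no more. The comparison in Section 2.13 is between randomized arms and does not need them.
- **That the trial cannot report MBD.** It can, by the alkaline phosphatase and phosphate rule.
- **That averaging is worth 20–50% more infants.** With within-infant share w, the mean of three has total variance (1 − w) + w/3. This is 0.833 at w = 0.25 and 0.667 at w = 0.50, hence factors of 1.20 and 1.50. But w is assumed, the comparator is a single-reading analysis that the article does not plan, and the intraindividual variation it mentions is not said to be reading-to-reading error.
- **That infant size and age bias the comparison.** Randomization balances them on average. Left unadjusted, they cost precision.

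**Conclusion.** The point holds as a correction to a secondary outcome. Speed of sound is mislabelled as bone mass, the averaging sentence is attached to the wrong measurements, two statements of MBD are unreconciled, and the planned comparison leaves the gestational-age strata unused.

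The mislabelling affects what may be concluded. It does not affect the validity of the randomized comparison. The loss of precision is real only so far as stratum predicts speed of sound. That is plausible from the article's own figures, but cannot be quantified from them. The 0.54 to 0.49 SD range assumes a reading for 54 to 65 infants per arm and describes the unadjusted comparison. The primary endpoint and the sample size do not depend on any of this.

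**What to change.** 1. In Section 2.8.2 and Table 1, name the outcome tibial speed of sound (m/s) at 35 weeks PCA. State one visit window: 2.8.2 gives ±1 week for the chemistry, while the Table 1 column holding the bone assessment gives ±2.
2. Move the averaging sentence so that it refers to the three speed-of-sound readings, and make the analysed value their mean.
3. In Section 2.13, compare arms on that mean as a continuous outcome in a linear model with arm and gestational-age stratum (24–28 versus 29–32 weeks). Report the adjusted mean difference with its 95% confidence interval. State that the adjustment is for precision.
4. Limit the ultrasound conclusion to speed of sound. Classify MBD occurrence by the stated biochemical definition, reconcile the conceptual definition with it, and say how osteopenia in the Abstract relates to it.

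The cost is a few sentences and one model term, or one degree of freedom. No new procedure, blood sample or infant is needed. The trade-off is a more modest claim about bone.

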#### 2.8.3. Parathormone

PTH is a peptide hormone that undergoes upregulation in response to hypocalcemia and vit D deficiency. It stimulates the reabsorption of calcium in the renal tubules, inhibits the excretion of phosphates, stimulates osteolysis of osteocytes and bone resorption by osteoclasts, and increases the absorption of calcium from the intestines [4]. Hyperparathyroidism may further worsen rickets through the promotion of osteolysis. Serum or plasma concentration of PTH in infants should be 10–40 pg/mL. Venous samples (0.3 mL) will be collected by neonatal staff for serum PTH concentration measurement at birth, at 28 ± 2 days of life, and at 35 ± 1 weeks of PCA, using the CMIA method by Abbot Alinity Analyzer. The calibration of the analyzer will be verified using suitable controls, in accordance with the product guidelines.

